#### Consent to Participate

Written informed consent will be obtained from all study participants or their legally authorized representatives prior to participation. The official informed consent form documents for Mbarara University of Science and Technology will be adopted for this purpose. Both trainee and patient participant informed consent documents are provided in Multimedia Appendix 1 and Multimedia Appendix 2, respectively. The ethical committees ruled that trainees involved in the data collection process at control centers do not need to provide any consent as this study will neither directly affect their practices nor collect their personal data.

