#### Strategies to Improve Adherence to the Intervention

The RTTDC is the intervention; thus, participants who do not attend all the modules and complete the posttraining MCQs will be excluded. Adherence to teachings in the RTTDC among care providers during clinical practice, such as the time taken from referral decision to execution and improper closed-loop communication leading to loss to follow-up, will be assessed as process measure outcomes.

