### Outcomes

This trial will examine both process measures and patient outcomes. The primary (process) outcomes of this trial will involve comparisons of (1) the time interval from the accident to hospital admission and (2) the time interval from the referral decision to hospital discharge between patients with motorcycle accident–related injuries presenting to the intervention centers and those presenting to the control centers.

The secondary (patient) outcomes of this trial will involve comparisons of (1) all-cause mortality at 90 days from the time of injury and (2) morbidity of motorcycle accident–related orthopedic and neurological injuries between patients presenting to the intervention centers and those presenting to the control centers. The morbidity of orthopedic injuries will be measured based on the Trauma Expectation Factor Score (TEFS) at admission and the Trauma Outcome Measure Score (TOMS) at 90 days as reported to outcome assessors [28]. On the other hand, for neurological injuries, the Glasgow Coma Scale (GCS) at admission and Glasgow Outcome Scale (GOS) at 90 days will be used as documented by the attending clinicians [29].

The tertiary outcomes will involve the effects of the training on provider knowledge based on pretraining and posttraining trauma-related MCQ scores and the barriers to injury care faced by providers during execution of definitive treatment. These will be determined in 2 ancillary studies that have been approved as part of this trial, and the protocols have been detailed elsewhere [25]. A summary of all outcomes and their case definitions, specific measurement variables, analysis metrics, methods of aggregation, and time points has been provided in Multimedia Appendix 3.

The patient outcomes were selected based on their validity and relevance in previous studies [7,30]. Further, level III evidence suggests that prolonged prehospital times may be associated with increased mortality among trauma patients [31]. However, it is unclear how these results relate to time-sensitive orthopedic and neurological injuries in LMICs that lack formal coordinated prehospital systems [32]. Thus, our process outcome measure variables were selected within the context of evidence-based practice. This practice stipulates that in accordance with the golden hour rule, a major trauma patient should be in the right place within 60 minutes following injury, otherwise there is a risk of mortality or morbidity [33].

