### Participant Timeline

Initially, cluster randomization of the trauma centers will be performed 3 weeks prior to commencement of the training to determine which centers will receive the training. Potential participants for the training will be screened for eligibility by the hospital and study administrators 2 weeks prior to the training, and eligible trainee participants will be consented and assigned to “rural trauma teams” of 6 members on the first day of the training, during which they will complete a pretraining questionnaire involving trauma-based MCQs. Subsequently, trainee participants will be followed up at 90 days (3 months) to complete posttraining MCQs. The first eligible patient participants at both control and intervention sites will be enrolled concurrently through a motorcycle trauma outcome registry (MOTOR) that will run parallel to the trial.

Informed consent, baseline sociodemographic and clinical characteristics, and prehospital intervals will be obtained at admission, and the GCS score will be determined. The TEFS will be obtained during the first week of admission or prior to discharge on the assumption that patients would have received their definitive surgical intervention or would have been referred for further care during this period. Further, the GOS score, all-cause mortality rate, and TOMS will be obtained at the 90-day follow-up. The GCS will be used to assess the level of traumatic brain injury in the acute phase, whereas the GOS will be used to determine neurological outcomes within the context of the level of independence at a later phase of traumatic brain injury [29]. On the other hand, the TOMS will be used to assess patient-reported trauma outcomes with reference to their expectations (TEFS) at the time of the trauma intervention in relation to the levels of pain, physical function, disability, injury treatment satisfaction, and overall satisfaction [28,30]. Throughout the study period, any individual patient barriers encountered during the pathway to execution of definitive injury care will be documented as summarized in the timeline presented in Multimedia Appendix 4.

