#### Methods for Additional Analyses

Subgroup analyses will be performed for (1) varying road user categories (pedestrian, passenger, and motorcyclist); (2) injury mechanisms (motorcycle-motorcycle accident, motorcycle-pedestrian accident, motorcycle-static object accident, and motorcycle-car accident); (3) varying injury severities (mild, moderate, or severe based on the KTS and GCS); and (4) multiplicity of serious injuries (one or multiple). To determine the training-effect heterogeneity across time periods, we will use an extension of Hussey and Hughes fixed effects model [49] for determining whether the intervention effect differs for each training period as summarized in the schematic representation of the study design (Multimedia Appendix 7).

For the ancillary study on provider outcomes, the difference in pretraining and posttraining mean scores will be computed with 95% CIs if the data are normally distributed; otherwise, the difference in median and IQR will be reported. For the qualitative ancillary study on the perceived barriers to injury care, directed content analysis of themes of transcribed data will be collated manually and presented as percentages.

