### Ancillary Studies

This trial has been approved with 2 ancillary studies. The first is a study to assess the effect of the RTTDC on provider knowledge, and the second is a qualitative study to assess the barriers to injury care as perceived by traffic police, medical trainee frontline workers, and individuals encountered in the real-time management of patient participants. The data collection team for the qualitative study will be surgery residents at the 6 regional referral hospitals who will be blinded to the cluster or treatment allocation. The results of the ancillary studies will be collected and analyzed separately and will be concealed from the trial team until the analysis of the main clinical trial findings is nearly complete. We hope that the findings of the ancillary studies will complement and inform the interpretation of the trial findings.

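### The ancillary knowledge outcome is described as an effect of the RTTDC, but the stated analysis estimates only the 90-day change in trained participants

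*Protocol article*

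**What the plan says.** Two sections of the protocol article word this outcome causally. Outcomes lists as tertiary "the effects of the training on provider knowledge based on pretraining and posttraining trauma-related MCQ scores". Ancillary Studies states: "The first is a study to assess the effect of the RTTDC on provider knowledge".

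Methods for Additional Analyses then gives the analysis: "the difference in pretraining and posttraining mean scores will be computed with 95% CIs if the data are normally distributed". For data that are not normal, it plans to report medians with IQRs. No contrast between arms is mentioned for this outcome.

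Participant Timeline places the pretest on the first day of training and adds that "trainee participants will be followed up at 90 days (3 months) to complete posttraining MCQs". Intervention Description, Participant Timeline and Strategies to Improve Adherence to the Intervention mention MCQs only for course participants. On control centers, Consent to Participate reports the ethics committees' ruling that "trainees involved in the data collection process at control centers do not need to provide any consent", because "this study will neither directly affect their practices nor collect their personal data".

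**The concern.** An effect of the course is the difference between the posttest score with the course and the score the same people would have had at that time without it. A pre-post difference replaces the second quantity with the score 90 days earlier. The two agree only if nothing else moves the score in between.

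Here other things could move it. Under Eligibility Criteria the medical and allied health trainees are in surgery and traumatology rotations, so they meet trauma cases and teaching between the tests. They also answer trauma MCQs twice. The trial has randomized control hospitals, but the analysis described for this outcome makes no use of them.

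What is at stake is interpretation. Ancillary Studies hopes that these findings will help in interpreting the main trial results. A knowledge gain labelled as an RTTDC effect could then be cited beside the patient results as showing that the training worked, which this contrast cannot show.

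**Working it through.** The article gives no sample size, SD or expected gain for the knowledge outcome, so there is no stated figure to reproduce. The check asks how often the planned interval would lie wholly above zero if the course itself added nothing.

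**Inputs from the article (Intervention Description)**
- Planned trainees: 66 + 12 + 30 + 140 + 264 = 512.
- All but the 66 traffic police are students, interns or residents: 446/512 = 87%.

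**Assumptions, not in the article**
- Course effect zero.
- Background gain g (rotation learning plus retesting) of 0 to 0.20 SD of a single MCQ score, the same for everyone.
- Pre-post correlation ρ of 0.3 to 0.7.
- Equal SDs at the two tests, approximately normal changes, independent trainees.

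**Formulas**
- SD of the change, in score SDs: √(2(1 − ρ)). This is 1.183, 1.000 and 0.775 for ρ = 0.3, 0.5 and 0.7.
- Noncentrality: δ = g√n / √(2(1 − ρ)).
- Chance that the 95% CI lies wholly above zero: P(T > t₀.₉₇₅,ₙ₋₁), where T is noncentral t with n − 1 degrees of freedom and noncentrality δ. For n = 512 the critical value is 1.965.

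**Example, g = 0.10, n = 512 (√512 = 22.63)**
- ρ = 0.3: δ = 0.10 × 22.63 / 1.183 = 1.91, chance 48%.
- ρ = 0.5: δ = 2.26, chance 62%.
- ρ = 0.7: δ = 0.10 × 22.63 / 0.775 = 2.92, chance 83%.

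**Results, n = 512, course effect zero**

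| Assumed background gain | Chance that the CI lies above zero (ρ 0.3 to 0.7) |
|---|---|
| 0 | 2.5% |
| 0.05 SD | 16-31% |
| 0.10 SD | 48-83% |
| 0.15 SD | 82-99% |
| 0.20 SD | 97-100% |

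The same calculation with 410 trainees (an assumed 80% of 512) gives 40-74% at 0.10 SD and 93-100% at 0.20 SD.

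**What this shows.** The pre-post estimate is off as an estimate of the course effect by exactly g, whatever the sample size. With about 500 trainees even a small g is likely to be separated from zero. A between-arm comparison of change would not have this problem. In a simulation with three hospitals per arm, zero course effect, score SD 15 points and ρ = 0.5, a cluster-level t test of change was significant (two-sided) in 4.8% to 5.7% of runs at every background gain from 0 to 5 points.

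**The case against.** **The detail may be elsewhere.** Outcomes says that the ancillary protocols are published separately, and they are not shown. They may contain a comparison group or a caveat. This is fair as to what the full study does. The point here rests on what the article itself states, though: a causal label in two sections and an uncontrolled analysis in a third.

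**A reader might infer that no control trainee was ever tested.** The documents do not say so. The consent passage concerns control-center trainees involved in data collection and does not mention MCQs. It points against control testing without excluding it.

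**A reader might infer that the result will very likely be positive even if the course teaches nothing.** The documents do not support that. It needs a background gain of about 0.15 SD or more, and no such figure is given. Some facts pull the other way. Sample Size puts the average student surgery rotation at 2 months, which is shorter than the 90-day interval. Trainees must already have met trauma concepts in clerkships. The 66 police officers have no clinical rotation.

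**A reader might also infer that dropping non-completers inflates the gain.** The adherence section says that "participants who do not attend all the modules and complete the posttraining MCQs will be excluded". That biases a paired change only if dropout is related to change, which nothing in the article shows.

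**No test is planned.** The article specifies an estimate with a CI and no decision rule for knowledge, and the trial's null hypothesis covers only time efficiency and injury outcomes. That stands, so the percentages describe how the interval would behave and are not the error rate of a planned test. The mismatch between label and estimate remains.

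**Conclusion.** The point holds in a limited form. Outcomes and Ancillary Studies promise an effect of the RTTDC on knowledge; Methods for Additional Analyses delivers a change over 90 days in trained participants, with no control-site scores described. That mismatch follows from the text and needs no numerical assumption.

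Its numerical consequence is conditional. It ranges from none, if there is no background gain, to an interval almost certain to lie above zero at a gain of 0.20 SD. The gain, the correlation and the independence of trainees are all assumptions.

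The priority is low. The outcome is tertiary, and Ancillary Studies has it analyzed separately and concealed from the trial team until the main analysis is nearly complete.

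**What to change.** In Outcomes, Methods for Additional Analyses and Ancillary Studies, restate the outcome as *change in MCQ score over 90 days among trained participants*. Add one sentence saying that, without a control comparison, it will not be reported as an effect of the RTTDC or used as evidence that the training worked. If the separate ancillary protocol does contain a control comparison, the article should say so and describe that analysis instead.

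The cost is a change of wording and a weaker claim for a tertiary outcome. Results gives August 27, 2023 as the last follow-up, so testing control-site trainees at the same time points is no longer possible. Modelling the pre-training gain by time in rotation is not recommended: the article does not show that rotation start dates were recorded, and such a model could not remove the retest gain.

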#### Methods in Analysis to Handle Protocol Nonadherence and Any Statistical Methods to Handle Missing Data

We will impute values for participants with missing end points, such as those lost to follow-up, those who withdraw consent, and those who crossover. The baseline sociodemographic and clinical characteristics of such participants will be compared between the intervention and control groups. For individual participants, crossover from the intervention group to the control group or vice versa for any reason will result in ultimate discontinuation from the trial.

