Imaging and blood transfusion services are often freely available at emergence units as government services but may be outsourced from private hospitals at a cost owing to long waiting times or service maintenance for CT scanners and X-ray machines. Finally, in terms of patient disposition, patients with minor injuries requiring surgery under local anesthesia are discharged on the same day. Moreover, patients with major trauma requiring conservative treatment, such as closed fractures, are treated in surgical wards, whereas those who are deeply unconscious or require critical care after major operations are admitted to the ICU until they are fit for care in general surgical wards prior to discharge. Alternatively due to overcrowding, often with higher bed occupancy rates exceeding the predetermined bed capacity, patients with major trauma may be referred to other centers, and the common reasons for referral include further neurosurgical evaluation with magnetic resonance imaging or further evaluation by a neurosurgeon, need for multiple specialty care and rehabilitation, and need for ICU admission elsewhere when local ICU beds are limited.

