### Data Collection and Management

#### Plans for Assessment and Collection of Outcomes

Data collection will start simultaneously at all the study sites. Medical officers (blinded outcome assessors) with a minimum qualification of Bachelor of Medicine and Bachelor of Surgery (MBChB) and at least 2 years of clinical experience will prospectively collect data through clinical observations, interviews, home visits, and extraction from hospital and police records. All outcome assessors must be willing to undertake a 1-day budgeted training in the use of data collection tools for this trial and the World Health Organization (WHO) ICD-10 online coding module. The data will be collected daily as medical trainees and interns will attend clinical rotations every day. Upon obtaining informed consent, the venue for data collection, including follow-up information, will be at accident and emergence departments during admission, surgical wards, and outpatient clinics, as well as through home visits and phone calls to patients, care takers, or recipient hospital physicians in the case of referrals.

The study variables will include sociodemographic and clinical variables, such as sex, age, injury mechanisms, including nature of collision and road user category, time of injury, prehospital transit time, prehospital care, mode of arrival, vital signs, nature of physical injuries, radiological findings, and injury severity based on the GCS score and Kampala Trauma Score (KTS) [43]. In addition, data on the nature of the treatment administered; need for referral; referral-exit interval; and outcomes, including the TOMS, GOS score, mortality, and time from injury to death, will be obtained. The data collection tools that will be used in this trial, such as the GCS, GOS, TEFS, TOMS, and KTS, have been shown to demonstrate excellent criterion internal validity, consistence, and reproducibility in previous studies [28,29,43,44].

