#### Plans to Promote Participant Retention and Complete Follow-Up

Coffee breaks will be facilitated during training to optimize participation. Phone and email contacts will be obtained from all medical trainees and law enforcement professionals. In addition, 2 phone contacts will be obtained for each patient participant at the time of enrollment at accident and emergency departments (ie, the patient and their next of kin or legally authorized representative who will in turn be provided with the phone contact of the study nurse coordinators for the purpose of follow-up). Automated reminders will be sent to data collection assistants through mobile phones and the research electronic data capture (REDCap) platform.

Where applicable, home visits will be conducted for participants who are unable to turn up for appointments because of their disability. Transport costs will be reimbursed for traffic law enforcement professionals and patient participants turning up for appointments outside of the routine hospital visits. Participants will be considered as lost to follow-up if they are untraceable by phone, clinic appointment, or home visit. Data on the baseline sociodemographic and clinical characteristics of those lost to follow-up or those who discontinue because of a breach of the intervention protocol will be retained for comparisons between groups, but the data of those who withdraw their consent will be deleted.

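### Withdrawn participants' data are to be deleted yet also imputed and compared, and patients who cross between arms are discontinued and imputed although their outcomes could be obtained

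*Protocol article*

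**What the plan says.** The section on protocol nonadherence and missing data contains three rules.

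- Imputation: "We will impute values for participants with missing end points, such as those lost to follow-up, those who withdraw consent, and those who crossover".
- Description of the same people: "The baseline sociodemographic and clinical characteristics of such participants will be compared between the intervention and control groups".
- Crossover of individuals: "crossover from the intervention group to the control group or vice versa for any reason will result in ultimate discontinuation from the trial".

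The section on participant retention and complete follow-up also says which data are kept. It keeps the baseline data of patients who cannot be traced, and likewise says that such data on "those who discontinue because of a breach of the intervention protocol will be retained for comparisons between groups". For withdrawals the same section takes the opposite course: "but the data of those who withdraw their consent will be deleted".

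The section on assessment and collection of outcomes lists the routes to follow-up information, which include "home visits and phone calls to patients, care takers, or recipient hospital physicians in the case of referrals". The section on concomitant care notes that "patients with major trauma may be referred to other centers". The article names no intention-to-treat or other analysis population.

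**The concern.** There are two separate problems.

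The first is a contradiction about withdrawals. One section has their records deleted. The other needs those records, both to describe the participants by arm and to impute their end points. Whoever prepares the data set must break one of the two rules, and one of them concerns what participants were told would happen to their data.

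The second is the crossover rule. Allocation is by hospital, so a patient's arm is fixed by the hospital at which he or she is enrolled, and a later move does not change it. Discontinuing the patient because of the move, and then replacing the 90-day outcome with an imputed value, creates missing data where a real value could have been obtained. The trigger occurs after randomization and may be related both to the patient's condition and to the referral process that the training addresses. If so, values imputed from patients who stayed may misstate the outcomes of those who moved, and by different amounts in the two arms.

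**Working it through.** **Withdrawals: the rules side by side**

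| Group | Retention section | Missing-data section |
|---|---|---|
| Lost to follow-up | Baseline data kept | Impute end point; compare baseline |
| Discontinued for protocol breach | Baseline data kept | Crossovers are discontinued; impute end point; compare baseline |
| Withdrew consent | Data deleted | Impute end point; compare baseline |

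The first two rows are compatible. The third is not. The retention sentence sets withdrawals apart from the other groups, so deletion cannot be read as covering only follow-up data while baseline data survive. With the record gone, the baseline comparison is impossible. An imputed end point could use none of the participant's own information; it would be a draw from other patients and add nothing.

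**Crossover: which outcomes can be affected**

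1. *Accident to admission (primary).* The Participant Timeline has prehospital intervals obtained at admission. The value exists before any transfer, so it is not affected.
2. *Referral decision to discharge (primary).* The data-collection section calls the variable a referral-exit interval. If the clock stops on leaving the first hospital, the value is also known before a crossover. If it runs to discharge from the receiving hospital, it can be lost. The text does not settle this, so the effect is possible but not certain.
3. *90-day mortality, GOS and TOMS (secondary).* All fall after a transfer, so discontinuation would leave them uncollected or unused. The planned contact with receiving hospitals, home visits and calls shows they were obtainable.

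**Numbers in the document**

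The only allowance for missing data is in the Sample Size section. It reproduces: 720 × (1 + 9 × 0.02) = 849.6, stated as 850; 850 × 1.18 = 1003, stated as approximately 1003. The 18% is for loss to follow-up. No crossover or withdrawal rate is given, and this point does not dispute the figure.

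**What the crossover rule could do (assumed inputs)**

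Let a fraction c of one arm (502 patients) cross over, let their true mean differ by D from that of patients who stay, and let imputation reproduce the mean of those who stay. The arm mean is then shifted by c × D. For the referral-to-discharge interval, with c and D assumed:

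| c | Patients | D = 1 h | D = 2 h | D = 3 h |
|---|---|---|---|---|
| 2% | 0.02 × 502 ≈ 10 | 0.02 h | 0.04 h | 0.06 h |
| 5% | 0.05 × 502 ≈ 25 | 0.05 h | 0.10 h | 0.15 h |
| 10% | 0.10 × 502 ≈ 50 | 0.10 h | 0.20 h | 0.30 h |

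All are well below the 1-hour difference that the plan calls clinically meaningful. For a proportion such as 90-day mortality the same formula applies with D as a difference in risk, and the shift cannot exceed c. The document supplies neither c nor D, so this shows scale only and is not an estimate.

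**The case against.** Several points on the other side have force.

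- *Referral is not crossover.* A reader might infer that the rule removes the most severely injured, because major trauma is what gets referred. The concomitant-care section does not say that the receiving centers are trial hospitals, still less hospitals in the other arm, and the trial includes only 6 of 17 regional referral hospitals. Follow-up through receiving physicians is planned, so referral alone does not discontinue a patient. This stands: referral counts only when it leads to a trial hospital in the opposite arm.
- *No intention-to-treat analysis is promised.* True. The rule departs from the principle and does not contradict a stated analysis set. Crossovers also remain in the comparison through imputation, though not on their own outcomes.
- *Only missing end points are imputed.* The text does not say that recorded values are overwritten. It does, however, list crossover as an instance of a missing end point and orders discontinuation, which is how the value becomes missing.
- *Crossover may mean trainees.* The trainee eligibility criteria do bar students from crossing arms. But end points, loss to follow-up and baseline clinical characteristics are patient terms, so the patient reading is the natural one.
- *Differential loss to follow-up.* The adherence section mentions "improper closed-loop communication leading to loss to follow-up" as a process measure. A reader might infer that missingness will differ by arm and that the plan is deficient without a sensitivity analysis. The document does not state that such a difference is expected, and sensitivity analyses and the imputation model may properly sit in an analysis plan that is not shown. No criticism is made on that ground.

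None of this reconciles the two rules on withdrawals, and an analysis plan could not silently reverse a stated deletion or discontinuation rule.

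**Conclusion.** The contradiction on withdrawals is established from the text alone: deletion on the one hand, imputation and baseline comparison on the other, cannot both be done.

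The crossover rule is workable but poorly chosen. It discards obtainable outcomes because of a post-randomization event and may bias the 90-day mortality, GOS and TOMS comparisons, and possibly the referral-to-discharge interval. The accident-to-admission interval is outside its reach. The size and direction of any bias are unknown because neither the number of crossovers nor their outcomes are given. It would be wrong to conclude that the whole missing-data section is unworkable, or that the trial's results are shown to be biased.

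The conclusion assumes that the crossover rule applies to patients and that the discontinuation rule was followed as written.

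**What to change.** Before the analysis, which the article places in Spring 2024:

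1. **Withdrawals.** Reconcile the retention section with the missing-data section, so that records deleted on withdrawal of consent are neither imputed nor included in the baseline comparison. Report the number of such withdrawals by arm.
2. **Crossovers.** Remove crossover from the reasons for imputation. Analyze every enrolled patient under the hospital of first presentation, use every outcome recorded whatever transfer followed, and impute only outcomes that are truly missing. Report the number of crossovers by arm.
3. **Limitation.** Last follow-up was on August 27, 2023. Outcomes never collected because a crossover patient was discontinued cannot be recovered by rewording. State how many there were and report this as a limitation.

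The cost is revised wording in two sections, submission of the amendment to the ethics committee that acts as data monitoring committee, and two counts by arm in the report. No new data collection is needed.
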